### Sample size

Because this study is based on clinical application, it is difficult to calculate the sample size through pre-experiments according to the actual situation; thus, the sample size of this study was finally determined based on the previous relevant literature data. The sample size outcome effect size was obtained from the literature using the ODI and VAS scores [29]. The mean change of the ODI in group A was approximately 92%, and the mean change of the VAS was approximately 0–3 points, while the mean change of the ODI in group B was approximately 85%, and the mean change of the NRS was approximately 4–5 points. The sample size was calculated using the sample size formula of the quantitative equivalence experiment *n* = 2(*Z*_*α*_ + *Z*_*β*_)^2^*δ*^2^/(*D* − *Δ*)^2^, assuming that *α* = 0.05 and *D* = 2.09 − 1.45 = 0.64, *δ*^2^ = [(0.56 + 0.78)/2]^2^ = 0.46 was obtained from literature retrieval, different values of *β* and superiority bounds were selected to calculate the sample size matrix, as shown in Table 1, and finally *n* = 50 was selected; taking into consideration a 20% dropout, thus 30 cases should be enrolled to each group, a total of 60 cases in two groups.

**Table 1 Tab1:** Sample size matrix

*α*	*β*	*D*	*δ*^*2*^	*Δ*	*n*
0.05	0.2	0.64	0.46	0.2	38
0.05	0.2	0.64	0.46	0.3	63
0.05	0.1	0.64	0.46	0.2	50
0.05	0.1	0.64	0.46	0.3	84

This trial is to be conducted in the Second Spine Department of the Fourth Clinical Medical School of Xinjiang Medical University, and hospitalized patients who meet the inclusion criteria will be included in the study. Because of the large number of patients undergoing OLIF in this department, it is possible to recruit sufficient subjects within the prescribed time; thus, an insufficient sample size is highly unlikely. In addition, there are benefits for patients participating in the study to supplement the sample size (e.g., free professional consultation, postoperative functional exercise instruction, and postoperative care consultation).

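### At the plan's own 20% dropout, enrolling 60 leaves 48 evaluable patients, not the 50 selected; the shortfall is small, and correcting it does not restore 90% power

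*Protocol article*

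**What the plan says.** All the figures are in the Sample size section of the protocol article and its Table 1.

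- Effect: "assuming that *α* = 0.05 and *D* = 2.09 − 1.45 = 0.64".
- Variance: the printed expression ends "0.56 + 0.78)/2]^2^ = 0.46 was obtained from literature retrieval".
- Choice of n: power and margin were varied to build Table 1, and "finally *n* = 50 was selected". The only row with that n reads "0.05 0.1 0.64 0.46 0.2 50", in the order α, β, D, δ², Δ, n. It therefore stands for 90% power with a margin of 0.2.
- Enrolment: "taking into consideration a 20% dropout, thus 30 cases should be enrolled to each group, a total of 60 cases".

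Under Dropout or loss to follow-up, the protocol allows patients to withdraw and the chief investigator to end a subject's participation. It removes these subjects' data from the final analysis.

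**The concern.** A dropout allowance protects the number of patients who can be analysed. Dropout is a fraction of those enrolled, so the required evaluable number must be divided by the fraction retained. The 60 in the protocol is exactly 50 × 1.2, which adds 20% of the evaluable number instead. The selected n, the dropout rate and the enrolment total then cannot all hold.

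Because withdrawn and terminated subjects are excluded, the evaluable number carries the power. A reader who takes the section at face value would expect 50 analysed patients after 20% loss and would be wrong. The same sentence also prints a variance expression that does not give the value beside it, so the table cannot be rebuilt from what is printed.

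**Working it through.** **Inputs (Sample size section and Table 1).** α = 0.05, D = 0.64, δ² = 0.46, Δ = 0.2, β = 0.1, n = 50, dropout 20%, enrolment 60 as 30 + 30.

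**Step 1: reproduce Table 1.** The printed formula is n = 2(Zα + Zβ)²δ²/(D − Δ)². The protocol does not say whether α is one- or two-sided. With two-sided α (1.96) and δ² = 0.46:

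| β | Δ | Computed | Table 1 |
|---|---|---|---|
| 0.2 | 0.2 | 37.3 | 38 |
| 0.2 | 0.3 | 62.5 | 63 |
| 0.1 | 0.2 | 49.9 | 50 |
| 0.1 | 0.3 | 83.6 | 84 |

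All four rows reproduce after rounding up. One-sided α gives 40.7 for the selected row and does not.

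**Step 2: the dropout step.**
- 50 × (1 + 0.20) = 60, the stated total.
- 50/(1 − 0.20) = 62.5, so 63, or 64 for equal groups.
- 60 × (1 − 0.20) = 48, or 24 per group.
- 1 − 50/60 = 16.7%, the largest dropout at which 60 still leaves 50.

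**Step 3: cost of this step in power.** This uses a two-sample t-test, two-sided 0.05, SD = √0.46 and difference D − Δ = 0.64 − 0.2 = 0.44. The noncentrality is 0.44/√(2 × 0.46/n), with n per group.
- n = 25: 0.44/0.1918 = 2.294, power 61.3%.
- n = 24: 0.44/0.1958 = 2.247, power 59.5%.

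The normal approximation, which is what the printed formula uses, gives 63.1% and 61.3%. The loss is about 2 points either way.

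**Step 4: why the level is about 60% and not 90%.** The formula's factor 2 makes n a per-group number. By the normal approximation, power is 90.0% at 50 per group. The protocol uses 50 as the total, so it has 25 per group before dropout is considered. On that approximation the split is:
- 50 to 25 per group: 90.0% to 63.1%, a loss of 26.9 points.
- 25 to 24 per group: 63.1% to 61.3%, a loss of 1.8 points.

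If the dropout step alone is corrected, 64 enrolled leaves 64 × 0.8 = 51.2 evaluable (25.6 per group), with power of about 64%. If 50 is read as per group, 50/0.8 = 62.5 gives 63 per group, 126 in total.

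**Step 5: the variance expression.** [(0.56 + 0.78)/2]² = 0.67² = 0.449, not 0.46. With 0.4489 the four rows become 36.4, 61.0 (60.96), 48.7 and 81.6, so 37, 61, 49 and 82. None matches Table 1. By contrast, (0.56² + 0.78²)/2 = (0.3136 + 0.6084)/2 = 0.461, which rounds to the 0.46 that does reproduce the table.

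**The case against.** The strongest reply is that this hardly matters. The shortfall is one patient per group. The 20% carries no stated source, and the break-even of 16.7% is close to it. No decision in the trial turns on 48 against 50. As to size, that stands, and the point should be read as a correction of stated figures.

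Second, the protocol never prints a multiplication by 1.2. That step is inferred from an exact match. This also stands, but the finding does not need it: 60 less 20% is 48 however the 60 was reached.

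Third, the per-group error is far larger, and if it is corrected the whole calculation has to be redone. That is true, but dropout would still have to be applied by division. Inflating 50 per group to 60 per group would again leave 48.

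Fourth, the mean-of-variances form is only plausible. The section does not say that 0.56 and 0.78 are standard deviations, and its source is not available here. That stands as well. What can be checked is that the printed expression is not 0.46.

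A reader might also infer that the dropout slip is what leaves the trial underpowered, or that enrolling 63 or 64 would give the selected 90%. The figures do not support either. The slip accounts for about 2 points, and 64 enrolled gives about 64% on the protocol's own inputs. Nor can the loss be made to look harmless by quoting power with no margin, because every row of Table 1 has a margin of 0.2 or 0.3.

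**Conclusion.** The point holds in a limited form. Taking 50 as the trial total, as the protocol does, 60 enrolled with 20% dropout gives 48 evaluable patients, 2 short. Fifty evaluable needs 62.5 enrolled, or a dropout of no more than 16.7%. The exclusion of withdrawn and terminated subjects means that the analysis does not make up the difference.

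The effect of this step is about 2 points of power. The fall from the selected 90% to about 60% is real on the protocol's inputs, but it belongs almost wholly to the use of a per-group n as a total.

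The variance misprint is minor and moves the selected n from 50 to 49.

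The power figures assume a two-sided α (inferred because it reproduces Table 1), a common variance of 0.46, a margin of 0.2 and equal loss in the two groups.

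**What to change.** Keep 60 and correct the sentence in one of two ways:
- state that 60 enrolled gives 48 evaluable (24 per group) at 20% dropout; or
- state that 60 leaves 50 evaluable if dropout does not exceed 16.7%.

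In either case quote power for the evaluable number. For 24 per group on the selected row this is about 60% (59.5% by t-test, 61.3% by the formula's normal approximation). If the per-group error is corrected and the sample size redone, apply dropout by dividing by 0.8.

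Print the variance expression actually used. If 0.56 and 0.78 are standard deviations, that would be (0.56² + 0.78²)/2 = 0.461. State that it was rounded to 0.46, since 0.461 unrounded gives 2 × (1.960 + 1.282)² × 0.461/0.44² = 50.04, which rounds up to 51.

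The cost is a corrected sentence and no extra patients. The disclosure is not slight, however: an honest restatement shows about 60% power where the selected row implies 90%, and the text should say that correcting the dropout step does not close that gap.

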### Inclusion, exclusion, and diagnostic criteria

The inclusion criteria are shown in Table 2, and exclusion criteria are presented in Table 3. All included patients who are indicated for surgery will be screened in strict accordance with the inclusion and exclusion criteria. The diagnosis of related diseases should be determined by physicians with extensive clinical experience based on the corresponding imaging examination, physical examination, and recognized standards and should be strictly controlled for accuracy in meeting the inclusion criteria and not meeting the exclusion criteria.

**Table 2 Tab2:** Inclusion criteria

1) Patients with grade I or II spondylolisthesis according to the examination
2) Those diagnosed as discogenic low back pain, disc herniation, or lumbar spinal stenosis by imaging examination
3) Those with pain caused by the disease that seriously affects daily work and life and is not relieved after a short period of conservative treatment
4) Those with a lesion responsible segment ranging from the second lumbar vertebra (L2) to the first sacral vertebra (S1) and a single responsible space
5) Those aged between 18 and 80 years
6) Those with a disease duration ≥ 6 months

**Table 3 Tab3:** Exclusion criteria

1) Patients with spinal fractures, spinal infections, and intraspinal tumors
2) Those who previously underwent spinal surgery
3) Those with osteoporosis (T < − 2.5), systemic autoimmune diseases, end-stage renal disease, and Parkinson’s disease
4) Those with combined major medical diseases not suitable for surgery
5) Those who suffer from mental illnesses that prevent them from communicating properly or from strictly following medical advice

### Randomization and blinding

Physicians [name] and [name], from the Fourth Affiliated Hospital of Xinjiang Medical University, will use computer software to generate random sequences, which will be sealed in envelopes. Eligible patients will be recruited by physicians of the department, [name] and [name]. The recruited patients will be randomized into two groups by [name], a physician of the department. In order to avoid the predictability of random sequences, the envelopes used are all of the same kind of envelope produced by the same manufacturer (that is, the appearance, thickness, texture are the same), and all sequences are not disclosed to recruiters and allocations. In this study, a single-blind approach will be adopted, that is, participants do not know which treatment they are receiving. The specific procedures performed will be kept confidential to all participants until unblinded.

To ensure the scientific accuracy of the study, it is also planned to charge the same fee for all subjects. The specific charges are as follows: preoperative preparation fee, surgery fee, anesthesia fee, cost of related equipment used during operation, and cost of intraoperative and postoperative drugs. In particular, the spinal orthoses used by the patients in the experimental group will be uniformly distributed by the research team to ensure that the spinal orthoses used by the patients in the experimental group are the same; thus, the cost of spinal orthoses will not be included. The total cost is RMB 55969.32.

### Intervention measures

The patients included in the research group will be randomized into two groups: group A (those undergoing OLIF + wearing spinal orthoses 3 days after surgery) and group B (those not suitable for spinal orthoses after surgery). VAS and ODI scores will be assessed and recorded for all patients 1 day before surgery. According to the inclusion criteria, all patients who undergo this procedure will have a single responsibility space and posterior four-screw implantation.

### OLIF surgical technique

Under general anesthesia, the patient is placed in the right lateral position and the surgical vertebral body is determined under X-ray fluoroscopy. With the responsible surgical space as the center, a surgical incision of approximately 6 cm is made along the body surface projection of the anterior edge of the upper vertebral body, the skin and superficial fascia are incised to bluntly separate external oblique, internal oblique, and transversus abdominis muscles, and the peritoneum is separated forward, which can reach the psoas muscle. The anterior space of the psoas major is bluntly separated with the fingers, and the psoas major is pushed dorsally to expose the surgical vertebrae. The automatic distractor is used for distraction, the camera source is installed, and the surgical intervertebral space is determined by fluoroscopy again. The annulus fibrosus is cut crossly with a sharp knife. The nucleus pulposus tissue and annulus fibrosus of the surgical intervertebral disc are removed using nucleus pulposus forceps. The intervertebral space is treated with different specifications of reamer in turn to break through the contralateral annulus fibrosus, and the intervertebral space is completely cleared to the bilateral cartilage endplate. The appropriate size of the test mold is selected. The intervertebral space is cleaned with saline and an interbody cage rich in allograft bone is implanted into the intervertebral space. A large amount of normal saline is used for flushing until there is no active bleeding, and gelatin sponge blood is filled. The fascia and subcutaneous tissue of the external oblique muscle is sutured using absorbable sutures layer by layer, and the wound is bound using medical adhesives.

**Fig. 2 Fig2:**
[figure not shown]
Spinal orthoses and manner of wearing

### Data collection

VAS and ODI scores are assessed 1 day before surgery and 2 weeks, 3 and 6 months, and 1 year after surgery, and BFS scores will be assessed at 1, 3, and 6 months and 1 year after surgery to comprehensively evaluate the therapeutic effect. The treatment regimen and effect evaluation are illustrated in Table 4.

**Table 4 Tab4:** Treatment regimen and effect evaluation

Data collection/recording	Person in charge	Observational phase	Interventions	Follow-up phase			
		1 day before surgery	Surgery	2 weeks after surgery	3 months after surgery	6 months after surgery	1 year after surgery
Obtaining informed consent	[name]	×					
Collecting patients’ basic information and medical history	[name] [name]	×					
Screen patients for eligibility	[name] [name]	×					
Interventions	[name]		×				
ODI	[name] [name]	×		×	×	×	×
VAS for pain	[name] [name]	×		×	×	×	×
BSF score	[name] [name]			×	×	×	×

*ODI*, Oswestry disability index; *VAS*, visual analog scale; *BFS*, Brantigan, Steffee, Fraser

### Main result measurement

A variety of outcome measures are used in this study, including the VAS (0–10 points) and ODI (0–50%), and are evaluated 1 day before surgery and 1, 3, and 6 months and 1 year after surgery. The ODI is used to assess disability associated with low back pain. The ODI has 10 questions about daily activities, including pain intensity, personal care, weight lifting, walking, sitting, standing, sleeping, sex, social life, and travel, each of which is rated on a scale of 0 to 5 points. The lower the score, the less affected the person is by pain. The VAS uses 0 points to indicate no pain and 10 points to indicate the peak of pain within the patient’s perception range, and the VAS is a self-assessment tool for pain consisting of 0 and 10 at either end of a straight line. Participants mark a point on the line to indicate their average pain level. The above two scales have been recognized by the medical community, and the value and effectiveness of the VAS and ODI scales have been demonstrated by related studies [30, 31]. The BSF score ranges from 0 to 4, where 0 points indicate no connection between the upper and lower parts of the vertebral body, height loss, and bone grafting absorption and 4 points indicate complete fusion and good shaping. The higher the score, the greater the degree of fusion. The main outcome measures in this study are the ODI, VAS, and BFS scores after follow-up and efficacy evaluation obtained as required. The above scores will be obtained by the designated personnel through follow-up visit. After obtaining the scores of the two, the efficacy is evaluated according to Table 4. Because the final efficacy evaluation of each patient is significantly affected by the above scores, which indirectly plays a decisive role in the results of the study, the relevant data should be obtained in strict accordance with the requirements during the follow-up process. The specific efficacy evaluation criteria are stated in Table 5.

**Table 5 Tab5:** Efficacy evaluation

	Efficacy			
	Cured	Significantly effective	Taking effect	Ineffective
Evaluation index				
ODI score	≤ 40%	40–59%	60–70%	> 70%
VAS score	< 2	2–3	4–5	> 5
BSF score	≥ 3	2	1	0

*VAS*, visual analog scale; *ODI*, Oswestry disability index; *BFS*, Brantigan, Steffee, Fraser

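### The stated ODI range of 0–50% contradicts the ODI bands in Table 5, and even on 0–100% ODI 40% has two categories and VAS marks between 3 and 4 have none

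*Protocol article*

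**What the plan says.** All the relevant text is in the protocol article, section Main result measurement, including Table 5.

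- Ranges: "A variety of outcome measures are used in this study, including the VAS (0–10 points) and ODI (0–50", followed by a percent sign.
- ODI construction: "The ODI has 10 questions about daily activities", with the scoring rule "each of which is rated on a scale of 0 to 5 points".
- ODI direction: "The lower the score, the less affected the person is by pain".
- VAS recording: "Participants mark a point on the line to indicate their average pain level".
- Table 5, ODI row, from *Cured* through *Significantly effective* and *Taking effect* to *Ineffective*: "ODI score ≤ 40% 40–59% 60–70% > 70" per cent.
- Table 5, VAS row, same order: below 2; 2–3; 4–5; above 5. BSF row: 3 or more; 2; 1; 0.

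The section names the three scores, together with efficacy evaluation, as the main outcome measures. It adds, speaking of this trial: "Because the final efficacy evaluation of each patient is significantly affected by the above scores, which indirectly plays a decisive role in the results of" (quotation cut short). It first sends the reader to Table 4 for the efficacy evaluation, but Table 4 is the visit schedule. Its last sentence gives Table 5 as the place of the criteria.

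**The concern.** A rule that sorts each patient into one of four efficacy categories needs a scale with a known unit, and exactly one category for every value on that scale. The ODI row has neither property as printed, and the VAS row lacks the second. An assessor who follows the text literally and one who converts to a percentage can put the same questionnaire at opposite ends of Table 5. Where a value has two categories or none, someone must decide case by case. If that happens after data are in, the share of patients called *Cured* depends on choices made with the outcomes in view.

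**Working it through.** **1. Which unit gives 50?** Maximum total = 10 items × 5 = 50 points. As a percentage of maximum, 50/50 × 100 = 100%. The printed 50 is reproduced as points but not as a percentage.

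**2. All 51 possible totals sorted into Table 5 under both readings.**

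| Category | Literal 0–50 | Total/50 × 100 |
|---|---|---|
| *Cured* only | 0–39 (40 values) | 0–19 points (20 values) |
| *Cured* and *Significantly effective* | 40 (1 value) | 20 points = 40% (1 value) |
| *Significantly effective* only | 41–50 (10 values) | 21–29 points = 42–58% (9 values) |
| *Taking effect* | none | 30–35 points = 60–70% (6 values) |
| *Ineffective* | none | 36–50 points = 72–100% (15 values) |

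Check: 40 + 1 + 10 = 51 and 20 + 1 + 9 + 6 + 15 = 51.

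On the literal range two of the four bands are empty. On 0–100% all four can be reached. Totals 21 to 50 (9 + 6 + 15 = 30 of 51) get a different category under the two readings. Example: 39 points is below 40, so *Cured* on the literal range; 39/50 × 100 = 78%, so *Ineffective* as a percentage. These are counts of scale values, not of patients.

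**3. What remains on 0–100%.** The upper limit of *Cured* and the lower limit of *Significantly effective* are both 40% and both are included, so a total of 20 points has two categories. The nominal gap between 59% and 60% is harmless: with ten items answered the percentage moves in steps of 2, from 58 to 60. With 7, 8 or 9 answered items and a denominator of 5 points per item, no total falls there either.

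**4. VAS row.** The score is a mark on a line, so values between whole numbers occur. The bands stop at 3 and resume at 4, so any mark strictly between them has no category. The documents do not give the reading precision. If marks are read to 0.1 (an assumption), the values 3.1 to 3.9 are unassigned, 9 of 101. If they are rounded to whole numbers, none is.

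**5. BSF row.** Scores 0, 1, 2, 3 and 4 each fall in exactly one category. No fault.

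**6. Could the ODI row mean percentage improvement?** No. Lower ODI is better by the protocol's own statement, and the lowest band is labelled *Cured*; as improvement the order would be reversed. The row applies to the absolute follow-up score. A patient who goes from 10 points (20%) before surgery to 19 points (38%) afterwards has worsened and still meets the ODI limit for *Cured*.

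**The case against.** The best defence is that the unit slip is transparent. Ten items of 0–5 points, and a table running past 70%, show that 0–100% was meant. The three scores are themselves main outcomes, the Statistical analysis section names no test on the Table 5 categories, and the sentence about a decisive role is loosely built and mainly asks for careful data collection. Much of this stands. It limits the damage but does not remove it: the 40% overlap and the VAS gap survive the charitable reading, and efficacy evaluation is still listed with the main outcome measures.

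Stronger readings are tempting, and the documents do not support them.

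- *Half the ODI categories can never be used.* True only on the literal 0–50%. On 0–100% every category is reachable.
- *The table puts nearly everyone in the top categories and cannot separate the groups.* This needs a distribution of post-operative scores, and none is given. The Sample size section quotes mean ODI changes of about 92% and 85%. Taken as improvement on 0–100%, they would put mean follow-up scores at no more than 100 − 92 = 8% and 100 − 85 = 15%, inside *Cured*. But the meaning of change is not defined there. The pain figures beside them (0–3 on the VAS for group A, 4–5 on the NRS for group B), read as scores, would fall in different Table 5 bands.
- *The categories must be based on change from baseline.* Absolute cut-offs are a design choice, not a contradiction.
- *There is no rule for discordant scales.* Such a rule may sit in the full protocol or analysis plan, which are not shown.

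**Conclusion.** The point holds for the ODI and VAS rows of Table 5, and not for the BSF row. Three faults are certain from the text alone: the range of 0–50% conflicts with bands up to and beyond 70%; ODI 40% has two categories on either reading; and VAS marks strictly between 3 and 4 have none unless scores are rounded, which the protocol does not say.

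In scale values, 30 of 51 ODI totals change category with the unit and one total is ambiguous on 0–100%. On the VAS, from 0 (whole numbers) to 9 of 101 values (steps of 0.1) are unassigned. The number of patients affected cannot be derived from the documents. The classification rule is wrong as written and should be corrected before any outcome is classified. The conclusion does not extend to a claim about the trial's ability to detect a difference.

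**What to change.** Before outcomes are classified, amend the section Main result measurement and Table 5:

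1. State ODI% = total/50 × 100, range 0–100%, in place of 0–50%.
2. Assign every boundary value once, for example ODI ≤40, >40 to <60, 60 to 70, >70; and VAS <2, 2 to <4, 4 to 5, >5. Leave the BSF row as it is.
3. Correct the pointer for the efficacy evaluation from Table 4 to Table 5.
4. Keep the ODI, VAS and BSF scores themselves as the main comparison, and report the categories as a secondary description, separately for each scale.

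Optional: report change from the pre-operative ODI and VAS beside the categories, so that a patient who worsens within the *Cured* band is visible.

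The cost is a short protocol amendment, since the Trial status section gives April 1, 2023 for recruitment. No new measurements are needed, because baseline and follow-up ODI and VAS are already scheduled. One check is needed: confirm whether ODI values already recorded are points or percentages, because a stored 38 could mean 38 points (76%) or 38% (19 points).

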**Fig. 1 Fig1:**
[figure not shown]
Study flow chart. OLIF, oblique lumbar interbody fusion; VAS, visual analog scale; ODI, Oswestry disability index; BFS, Brantigan, Steffee, Fraser

The main outcome measures include the Oswestry disability index (ODI), visual analog scale (VAS), and Brantigan, Steffee, Fraser (BSF) to assess pain intensity [28]. The clinical outcomes of these patients will be assessed using ODI and VAS scores 1 day before surgery and 2 weeks and 3, 6, and 12 months after surgery, and BFS scores will also be assessed starting from 2 weeks after surgery.

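### ODI, VAS and BSF are all main outcomes with no ranking, decisive visit or success rule, while the sample size rests on one difference whose scale and visit are not stated

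*Protocol article*

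**What the plan says.** **Outcomes.** The Main result measurement section states: "The main outcome measures in this study are the ODI, VAS, and BFS scores after follow-up and efficacy evaluation obtained as required". Methods/design lists the same three together: "The main outcome measures include the Oswestry disability index (ODI), visual analog scale (VAS), and Brantigan, Steffee, Fraser (BSF) to assess pain intensity". The article describes no secondary tier.

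**Visits.** The lists differ:
- Methods/design has ODI and VAS at "1 day before surgery and 2 weeks and 3, 6, and 12 months after surgery", with BSF from 2 weeks onward. Table 4 agrees.
- The Data collection text gives the same visits for ODI and VAS, but "BFS scores will be assessed at 1, 3, and 6 months and 1 year after surgery".
- Main result measurement says VAS and ODI "are evaluated 1 day before surgery and 1, 3, and 6 months and 1 year after surgery".
- The Abstract has 2 weeks and 1, 6 and 12 months.

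Each list has four post-operative visits, and none is singled out.

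**Sample size.** The effect size is said to come from the literature on ODI and VAS. The section then gives an ODI change of about 92% and a VAS change of about 0–3 points for group A, whereas "the mean change of the ODI in group B was approximately 85%, and the mean change of the NRS was approximately 4–5 points". The calculation itself proceeds by "assuming that *α* = 0.05 and *D* = 2.09 − 1.45 = 0.64", with variance 0.46. From Table 1 it selects n = 50 (β = 0.1, Δ = 0.2). BSF has no sizing input.

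**The concern.** The choice of primary outcome and time point tells a reader which result answers the trial's question. Here three scores share that role at every visit. They measure different things: disability, pain and radiographic fusion. They could easily disagree, and the protocol does not say what would then be concluded about the orthosis.

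The sample size section would normally settle the matter by showing which comparison the trial was built for. It does not, because D carries no unit or visit and does not match the figures around it. The planned 90% power therefore belongs to no named test, and the conclusion could be drawn from whichever comparison looks favourable once the data are in.

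**Working it through.** **1. Reproduce the plan's figure.** Inputs from the Sample size section: α = 0.05, β = 0.1, D = 0.64, variance 0.46, Δ = 0.2. The printed formula is n = 2(Zα + Zβ)² × variance / (D − Δ)².

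n = 2 × (1.960 + 1.282)² × 0.46 / 0.44² = 49.9, so 50.

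The other rows of Table 1 (38, 63, 84) also reproduce with 1.960, the two-sided 5% value. The whole 0.05 is spent on one comparison.

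**2. Can D be traced to the quoted values?**
- ODI: 92% − 85% = 7 percentage points, not 0.64.
- VAS against NRS: the gap between 0–3 and 4–5 is at least 4 − 3 = 1 and at most 5 − 0 = 5, so it always exceeds 0.64. Neither 2.09 nor 1.45 lies in the 4–5 range given for group B.
- If these changes are reductions in pain, group B improves more, against the hypothesis in the Assumption section.
- The NRS is not in Table 4 or any other assessment list.

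**3. Count the comparisons.** 3 scores × 4 visits = 12. The efficacy categories of Table 5 are not counted.

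**4. If success on any one test counts.** The chance of at least one false positive with k independent two-sided tests at 0.05 is 1 − 0.95^k:
- k = 3: 1 − 0.95³ = 0.143
- k = 12: 1 − 0.95¹² = 0.460

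Scores on the same patients are correlated, and the documents give no correlations. With an assumed equal correlation between the test statistics:

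| Tests | ρ = 0 | ρ = 0.5 | ρ = 0.7 |
|---|---|---|---|
| 3 scores, one visit | 14% | 13% | 11% |
| 3 scores, 4 visits | 46% | 32% | 23% |

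These count false positives in either direction. Counting only those that favour the orthosis, 12 independent tests give 1 − 0.975¹² = 0.26, against a nominal 0.025.

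**5. If all three must succeed at one visit.** The false-positive rate stays at or below 0.05. If each test had the planned 90% power, joint power would be 0.9³ = 0.73 with independent tests. It would approach 0.90 only as the tests became perfectly correlated.

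**6. Cost of keeping several primaries.** The same formula, with D, variance and Δ assumed to apply to every score, at 90% power:
- α = 0.05/3 = 0.0167, Z = 2.394: n = 2 × (2.394 + 1.282)² × 0.46 / 0.44² = 64.2, so 65.
- α = 0.05/12 = 0.00417, Z = 2.865: n = 81.7, so 82.

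Both compare with 50 for one outcome at one visit, before dropout. Whether 50 is a per-group or a total number is a separate question, not counted here.

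**The case against.** The strongest reply is that the 12 tests are not in the protocol. α = 0.05 appears only as an input to the sample size formula. The Statistical analysis section names one between-group test, a chi-square for adverse events. No section says that each score is tested at each visit at 0.05, or that one significant result is enough. That stands. A reader might infer that the trial has a 46% false-positive rate, or that its α is already broken. The documents do not support this: the inflation follows only under an any-success rule, and 46% also needs independence, which is implausible for repeated scores on the same patients.

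A reader might also infer that D belongs to no outcome at all. That is too strong. The Sample size section names ODI and VAS jointly, and means near 2 with standard deviations of 0.56 and 0.78 look more like a 0–10 scale than a percentage. VAS is a plausible reading, but it is not stated, and no visit is given.

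Finally, multiplicity methods and test models are commonly left to an analysis plan, which is not shown. Their absence is not the point here. Which outcome and visit are primary is a protocol decision, and this protocol has made it by giving three scores equal standing. An analysis plan that named one would be overriding the protocol, not completing it.

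**Conclusion.** The point holds as a defect in how the protocol defines success. Three unranked main outcomes, no decisive visit and no rule for combining them sit beside a sample size built on one difference whose scale and visit are not stated and which its neighbouring figures do not yield.

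The consequence depends on a rule that the protocol does not give. Under any-success, the false-positive chance is roughly two to three times the nominal 5% for three scores at one visit, and about five to nine times for all 12 comparisons. Under all-must-succeed, α is protected but the planned 90% power is not reached. In neither case are both design figures as stated. The sizes rest on assumed correlations of 0 to 0.7 and on counting four visits.

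That "main" is not literally "primary" makes little difference, since there is no other tier.

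**What to change.** Before any outcome comparison, name one primary outcome at one visit, for example 12 months as the end of follow-up. Choose the scale from which D = 0.64 and its variance were taken, and label the other scores and visits secondary. This keeps α = 0.05 and the Table 1 figure of 50.

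If all three scores must stay primary, fix one visit and use Holm across them. The power cost should be acknowledged: Bonferroni, which is also Holm's first step, needs about 65 rather than 50 by the protocol's own formula.

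In the Sample size section, state the scale and visit of D and reconcile it with the quoted ODI, VAS and NRS values. Deleting those values would only hide the mismatch. Bring the visit lists in the Abstract, Methods/design, Data collection, Table 4 and Main result measurement into agreement, so that the chosen visit exists in all of them.

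The cost is protocol and registry wording, and the demoted outcomes become supportive. Trial status dates recruitment from April 2023, so the change may fall during the trial. It should be dated and made without sight of results by group.

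Adjusting the ODI and VAS comparisons for the pre-operative score already collected would be a free gain in precision, but it is optional and not part of the error.
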